## Abstract

**Background:**

Aortic stenosis (AS) and mitral regurgitation (MR) are common cardiac conditions associated with significant morbidity and mortality if left untreated. Despite the availability of effective therapies, many patients with severe AS and MR do not receive timely interventions, with disparities particularly affecting minority populations, women, and those in rural areas.

**Methods:**

The Addressing undertreatment and heaLth Equity in aortic stenosis and mitral regurgitation using an integrated ehR plaTform (ALERT) study is a multicenter, prospective, cluster-randomized controlled trial designed to evaluate the impact of automated electronic health record notifications on the management of severe AS and MR. This cluster-randomized controlled trial involves at least 5 US hospital systems. Providers are randomized to receive automated notifications or not receive notifications, based on echocardiogram report findings. The primary end point is a hierarchical composite of transcatheter or surgical valve intervention (valve intervention) or multidisciplinary heart team clinic visit within 90 days. The study aims to randomize at least 600 providers and 1500 total patients 1:1 into each study arm, hypothesizing that automated notifications increase the proportion of patients receiving appropriate evaluation and treatment.

**Results:**

The results of the study are pending completion of enrollment and should be available in Q2 2026.

**Conclusions:**

The ALERT study leverages integrated electronic health record platforms to address undertreatment in severe AS and MR, with the potential to improve patient outcomes and reduce disparities in care.

## Introduction

Aortic stenosis (AS) and mitral regurgitation (MR) are prevalent cardiac valvular conditions that pose significant health risks if left untreated.^1^ The AS is highly prevalent among older adults, and estimates suggest that nearly half of the patients with symptomatic severe AS do not receive aortic valve replacement (AVR).^2^ The average life expectancy of those left untreated after the onset of symptoms is approximately 2 years, underscoring the critical need for timely intervention.^3^ Similarly, MR, which affects 2% to 10% of the general population and increases with age,^3^ is often underdiagnosed and undertreated. It is estimated that up to 50% of patients with symptomatic severe MR do not receive surgical or transcatheter intervention,^4^ resulting in a poor prognosis with a median life expectancy of only 5 years following symptom onset.^5^

Treatment gaps for AS and MR are even more pronounced in racial and ethnic minority populations. Although minorities represent approximately 20% of the US population over the age of 75 years,^6^^,^^7^ only 9% of transcatheter aortic valve replacement (TAVR) patients self-identify as being a minority.^8^ Factors, such as lower disease prevalence reported in minority populations, may contribute to differences in AVR utilization, but do not fully explain the treatment gap.^9^, ^10^, ^11^ Additionally, underutilization of TAVR has been reported among women^12^ and patients living in areas with lower population density.^13^ Multiple reasons for the lower rate of referral and treatment have been cited, including provider specialty, differences in disease prevalence, patient characteristics, health care access, bias, and health care system factors.^11^^,^^14^^,^^15^ Therefore, there exists a need to better identify patients with AS and MR who are potential candidates for surgical and transcatheter therapies to ensure they are evaluated and, when warranted, treated in a timely manner.

The Addressing undertreatment and heaLth Equity in aortic stenosis and mitral regurgitation using an integrated ehR plaTform (ALERT) study^16^ aims to evaluate how electronic health record (EHR) platforms can be leveraged to address the undertreatment of patients with severe AS and moderate-to-severe or severe MR. The ALERT study will enroll patients from at least 5 US hospital systems with racially and ethnically diverse populations. Patients will be included in the study if they have either severe AS or moderate-to-severe or severe MR and are considered not managed for their disease at the time of their echocardiogram. The end point will be a hierarchical composite of transcatheter or surgical valve intervention or multidisciplinary heart team (MHT) clinic visits within 90 days from the date the notification goes out or would go out.

## Materials and methods

### Study design

The ALERT study is a multicenter, prospective, cluster-randomized controlled trial designed to evaluate the impact of automated notifications on the identification and management of patients with severe AS or moderate-to-severe or severe MR. This study involves at least 5 US hospital systems and will focus on patients who are potentially suboptimally managed insofar as they have not undergone procedural treatment or been referred to an MHT. Providers, including doctors and advanced practice providers, will be randomized to either receive automated notifications or not receive notifications for the duration of the study, ensuring a reduction in cross-contamination and enhancing the precision of the alert intervention (Figure 1). Notifications will be delivered based on an algorithm to the most appropriate provider, aiming to spur timely follow-up evaluations and interventions (Figure 2). The study’s primary end point will be a hierarchical composite of time to transcatheter or surgical valve intervention or MHT clinic visits from the date the notification goes out or would go out. The rationale for the 90-day observation window is that a shorter time frame facilitates easier inference of causality regarding the effectiveness of the notification, and it aligns with recent performance and quality measures outlined for AS and MR.^17^ Additionally, the hierarchical composite end point ensures that even if some patients are not immediately indicated for a valve intervention, prompting a referral for MHT evaluation is consistent with professional guidelines.^18^

**Figure 1 fig1:**
[figure not shown]
**Randomization process.** Providers will be randomized in 2 tranches. The first tranche will be providers for whom retrospective data on their historical echo volumes are available. These providers will be stratified by their historical echo volume. Randomization will be 1:1 into control and notification arms within the echo volume strata. The second tranche will be providers randomized 1:1 upon ordering an echo for an eligible patient. Providers stay in their respective study arm for the duration of the study. Only patients who meet the eligibility criteria are included in the study, and providers only receive notifications on those patients.

**Figure 2 fig2:**
[figure not shown]
**Upon the date of the echocardiogram or the discharge date, for outpatients and inpatients, respectively, decision criteria are run to determine the provider assigned to the patient for the study.** For outpatients, it is the ordering provider; for inpatients, a hierarchy is considered to prioritize a cardiologist or a primary care provider (PCP). Once the provider is assigned to the patient, they are randomized into study arms if they have not yet been randomized. The randomization of the provider dictates the randomization of the patient. I/E, inclusion/exclusion.

The study duration spans from the date of the first patient enrollment to the date of last follow-up and study completion. The patients’ monitoring window starts between 1 and 5 days after the echocardiogram (for outpatients) or after the discharge date (for inpatients). This is henceforth referred to as the index date. The specific day the notification is sent is when the monitoring window begins and is determined by the participating site and set in the software.

The study will be conducted according to good clinical practice principles, and it conforms to the Declaration of Helsinki. The study protocol was reviewed and approved by an independent institutional review board (IRB) before study initiation and will continue to be reviewed by the IRB for the duration of the study (Advarra IRB Pro00071710). A waiver of consent for the patient and provider will be obtained by the central IRB. Each site will be given the autonomy to bring awareness of the study to providers who might receive a notification. This autonomy was purposefully allowed to aid in implementation and take into account differing practice patterns with regard to referral and institutional governance, with the understanding that each site will adhere to the study protocol. The majority of the sites conducted an “awareness communication campaign” that included an IRB-approved informational letter with opt-out instructions. However, one site elected to forgo any prestudy communication at all and started alerting without warning. This approach was approved by their institution's IRB. Each site implemented this process by its own design, and it was the site principal investigators’ responsibility to align with their IRB and strategy for their institution. All study sites follow and comply with the principles of the Declaration of Helsinki, 21 CFR Part 11 (electronic records, electronic signatures), the clinical trial agreements, the procedures described within this clinical investigation plan, and local ethical committee requirements. The study will be conducted according to federal, national, and local laws, regulations, standards, and requirements of the countries where the study was conducted. The ALERT study is registered at ClinicalTrials.gov (NCT06099665).

### Study and site oversight

This study utilizes a steering committee that advises on the scientific content of the study and provides input for study execution, aiming to provide unbiased opinions and expertise to the clinical study design and process. Each participating site designates a site principal investigator to oversee the execution of the study at their site. Medtronic’s research divisiempus and the steering committee with expert guidance, protocol review and validation, study design, peer review of the analysis programming, and final analysis validation. It should be noted that Medtronic is providing funding for this study in a collaborative research arrangement with Tempus AI. For clarity, Tempus AI is the sponsor of the study. Medtronic’s involvement also includes providing scientific input and oversight through its research division, including protocol review, analysis validation, and participation in the steering committee.

### Study objective and hypothesis

The study aims to test whether the use of automated notifications will affect the proportion of patients who are appropriately evaluated and, when warranted, treated with a valve intervention.

Our hypothesis is that patients with severe AS or moderate-to-severe or severe MR who are in the care of physicians receiving the automated notifications will be more likely to undergo a valve intervention or have a clinic visit with the MHT within 90 days compared to those whose physicians do not receive the notifications (Central Illustration).

**Central Illustration fig5:**
[figure not shown]
**A randomized trial evaluating the impact of automated notifications on the identification and treatment of patients with aortic stenosis (AS) and mitral regurgitation (MR): Design of the ALERT study.** MHT, multidisciplinary heart team; PCP, primary care provider.

### Study population

Patients who meet 1 or more criteria for severe AS or moderate-to-severe or severe MR (Table 1), but do not have an associated follow-up visit scheduled with a cardiologist member of the MHT, cardiovascular surgeon, or have a valve intervention scheduled, will be included in the study. Patients with both AS and MR will have an alert sent for AS first. Patients must be at least 18 years old and have an echocardiogram ordered by a provider who is not part of the MHT nor a cardiac surgeon. Patients with a nonnative aortic or mitral valve (bioprosthetic or mechanical) will be excluded if that nonnative valve was identified with criteria for disease, because this study is specifically designed to evaluate care pathways for patients with native valve disease, given that concerns about undertreatment have primarily focused on this population. However, if a patient is identified with AS but has a mitral valve prosthesis, they will still be considered for the study. The opposite scenario, with a patient identified with MR but having an existing AS prosthesis, is true as well. The exclusion occurs if the target valve identified with disease has been previously treated with a therapeutic device or procedure. In addition, patients already scheduled for a recent valve intervention or a clinic visit with the MHT are excluded from the study (Table 2). This includes recent visits in the past, after the study start date, or future visits or procedures already scheduled for the patient.

**Table 1 tbl1:** Inclusion criteria.

At least 1 of the following 3 options for aortic stenosis and/or the single option for MR is determined from echocardiogram findings: 1. AVA or DI (patients with either AVA or DI measured in their echo, as well as at least 1 hemodynamic measure above the minimum threshold) a. Either: i. AVA ≤1.0 cm^2^ ii. DI ≤0.25 b. And any of i. Aortic mean gradient ≥15 mm Hg ii. Aortic peak gradient ≥30 mm Hg iii. Aortic jet velocity ≥2.75 m/s 2. AVA + other (patients with AVA and at least 1 other echo measurement in their echo above the threshold) a. 1.0 cm^2^ < AVA ≤ 1.2 cm^2^ b. And any of: i. Aortic mean gradient ≥40 mm Hg ii. Aortic peak gradient ≥64 mm Hg iii. Aortic jet velocity ≥4.0 m/s 3. POSSIBLE (possible aortic stenosis, but requires human review) a. AVA is null or >1.2 cm^2^ b. And any of: i. Aortic mean gradient ≥ 40 mm Hg ii. Aortic peak gradient ≥ 64 mm Hg iii. Aortic jet velocity ≥4.0 m/s Or a. Either i. AVA ≤1.0 cm^2^ ii. DI ≤0.25 b. And all are: i. Aortic mean gradient <15 mm Hg ii. Aortic peak gradient <30 mm Hg iii. Aortic peak velocity <2.75 m/s Any patient flagged for "POSSIBLE" does not result in automatically notifying the provider; instead, a notification is sent to the Tempus research team for manual review in conjunction with the site principal investigator, and if requested by Tempus or the site principal investigator, a steering committee member. If clinical confirmation is received for severe aortic stenosis from the site principal investigator, a notification is sent to the provider. 1. MR a. Mention of severe MR or moderate-to-severe MR (based on a qualitative characterization of MR severity and not based on quantitative measurements) Any patient mentioned with only moderate MR or a lesser severity will be excluded.

AVA, aortic valve area; DI, dimensionless index; MR, mitral regurgitation.

**Table 2 tbl2:** Exclusion criteria.

Exclusion criteria: 1. Age <18 y. 2. The patient had evidence of a prior transcatheter or surgical repair or replacement of the target valve. 3. The echocardiogram was ordered by a cardiologist on the MHT or a cardiac surgeon. 4. Patient already has a scheduled clinic visit with a member of the MHT or a recent (since the start of the study at that site) clinic visit with the MHT, or a scheduled transcatheter or surgical valve intervention in the future.

MHT, multidisciplinary heart team.

### Sample size

Based on retrospective data within the Tempus Next database (Tempus AI, Inc), a cloud-hosted, HIPAA-compliant, artificial intelligence–enabled care pathway platform that notifies providers of deviations from guideline-based care, it is estimated that 35% of patients with severe AS or moderate-to-severe or severe MR will meet the criteria for the study. The exclusion of managed and treated patients, and the 90-day observation window, resulted in an expected incidence of the end points to be 5% and 10% for valve intervention and MHT, respectively. Given these assumptions, the study has 82% power to detect a 5% absolute increase in the proportion of patients who receive MHT follow-up or valve intervention within 90 days with a sample size of 1246 patients and 500 providers/clusters.

The power of the study was determined through simulations using exponential distributions for the time to valve intervention and referral to MHT within a Gumbel-Hougaard copula. The simulations assumed an absolute effect of the notifications on the rate of valve intervention or referral to MHT, increasing their incidence within 90 days by 5%. The study aims to randomize at least 600 providers, caring for 1500 total patients, 1:1 into each study arm across 5 sites in the US.

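### The 82% power is stated for a 5-point rise in the composite, but the simulation described most naturally raises each component by 5 points, and the two agree only under strong dependence

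*Protocol article*

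**What the plan says.** All the figures are in the Sample size section of the protocol article. The retrospective data "resulted in an expected incidence of the end points to be 5% and 10% for valve intervention and MHT, respectively". The first paragraph then concludes that "the study has 82% power to detect a 5% absolute increase in the proportion of patients who receive MHT follow-up or valve intervention". This effect is on a single proportion: patients with either event by day 90. The size behind that figure is 1246 patients in 500 provider clusters.

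The second paragraph says that power came from simulating exponential times to each event, joined by a Gumbel-Hougaard copula. The simulated effect was "an absolute effect of the notifications on the rate of valve intervention or referral to MHT, increasing their incidence within 90 days by 5" (percent). The recruitment target is larger than the size behind the 82%: "The study aims to randomize at least 600 providers, caring for 1500 total patients, 1:1 into each study arm".

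The section Study objective and hypothesis also frames the aim as a proportion: whether notifications "affect the proportion of patients who are appropriately evaluated and, when warranted, treated with a valve intervention". Under Statistical considerations, the primary test is a stratified win ratio that ranks valve intervention above the MHT visit.

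**The concern.** The plural in "increasing their incidence within 90 days by 5" (percent) follows two separately listed incidences, and the model has two separate event times. The natural reading is therefore +5 points on each component. Unless the two events overlap almost completely, that is a larger effect than +5 points on the composite, and it doubles the rate of valve intervention.

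The 82% is what readers will use to judge how sensitive the trial is. If it belongs to the larger effect, the printed sentence overstates the chance of detecting the smaller one. A gain that comes mainly through MHT visits has the least power. That case is plausible, since the Study design section accepts that some patients are not immediately indicated for intervention.

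**Working it through.** **Inputs from the article.** Control incidences are 5% (valve) and 10% (MHT). There are 1246 patients, so 623 per arm, and 500 providers, so 1246/500 = 2.49 patients each. The target is 1500 patients, 750 per arm. The model is exponential times with a Gumbel-Hougaard copula, 90-day follow-up and a win-ratio test.

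**Assumptions, because the article does not give them.** Two-sided 0.05, with one-sided 0.05 as a variant. Copula parameter θ from 1 (independence) to 30 (near-complete dependence). No clustering at first. The win ratio is unstratified.

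**Step 1: composite gain if each component rises 5 points.** Composite = 1 − exp{−[a^θ + b^θ]^(1/θ)}, with a = −ln(1 − valve incidence) and b = −ln(1 − MHT incidence).

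- θ = 1: control 1 − 0.95 × 0.90 = 14.5%; notified 1 − 0.90 × 0.85 = 23.5%; gain 9.0 points.
- θ = 2: control a = 0.0513, b = 0.1054, composite 11.1%; notified a = 0.1054, b = 0.1625, composite 17.6%; gain about 6.6 points before rounding.
- θ = 3: gain 5.8. θ = 5: gain 5.3. θ = 10: gain 5.0 (10.0% to 15.0%).

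**Step 2: can the 82% be reproduced?** Not uniquely. Simulated win-ratio power at 623 per arm (1500 trials per cell, two-sided 0.05, no clustering):

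| θ | Each component +5 | Composite +5, equal increments | Composite +5, common hazard ratio | Composite +5, MHT only |
|---|---|---|---|---|
| 1 | 99% | 69% | 64% | 60% |
| 2 | 94% | 75% | 74% | 71% |
| 3 | 90% | 75% | 75% | 69% |
| 5 | 81% | 80% | 77% | 71% |
| 10 | 79% | 80% | 75% | 74% |
| 30 | 79% | 80% | 75% | 73% |

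Repeat runs with fewer trials differ by about 2 points, so the last three columns are summarised as about 59-80%. With each component +5, 82% is matched near θ = 5 without clustering. With provider-level log-normal frailty, 250 providers per arm and a cluster-robust variance, it is nearly matched at θ = 1 with frailty SD 1.0 (83%) and at θ = 3 with SD 0.5 (81%).

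**Step 3: two-proportion check of composite +5.** Power = Φ{[Δ − 1.96√(2p̄(1 − p̄)/n)] / √([p₀(1 − p₀) + p₁(1 − p₁)]/n)}, with Δ = 0.05.

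- n = 623, 10% v 15%: (0.05 − 1.96 × 0.01874)/0.01869 = 0.71, power 76%.
- n = 623, 15% v 20%: (0.05 − 1.96 × 0.02153)/0.02148 = 0.36, power 64%.
- n = 750, same pairs: 83% and 72%.

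**Step 4: clustering.** As an illustration, take a design effect of 1.2. With 2.49 patients per provider this needs an intracluster correlation of 0.2/1.49 = 0.13. The check falls to 56-68% at 1246 patients and 64-76% at 1500.

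**Step 5: where composite +5 does reach 82%.** With the whole gain in valve intervention and strong dependence, win-ratio power is about 85-89% without clustering. With one-sided 0.05 and no clustering, the composite +5 scenarios in the table give about 71-88%.

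**The case against.** The strongest reply is that the article never states that each component rises by 5 points. Both sentences join the two events with an or, so they may describe one effect. That stands: the per-component reading is an inference, though the more natural one.

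Strong dependence is also plausible, since the Discussion describes referral to the MHT followed by intervention as one pathway. At θ of 5 or more the two descriptions nearly coincide, and power is about 79-82% before clustering. This stands too, but clustering would lower it, and it still requires valve interventions to double, which the section does not say.

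The shortfall further depends on an assumed two-sided 0.05. The hypothesis is directional, and a one-sided 0.05 test would bring 82% into range. The planned 1500 patients also recover part of any loss.

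A reader might infer that the 82% is an arithmetic error or that the trial is underpowered. The documents support neither, because several combinations of inputs that the article does not print are consistent with 82%. The absence of alpha, intracluster correlation and copula parameter from a condensed article is not a fault. Listing the composite proportion as a further secondary outcome would be a preference, not a correction.

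**Conclusion.** The point holds as an inconsistency in a power figure that readers will rely on. The effect attached to the 82% and the effect described for the simulation are the same only under strong dependence; otherwise the simulated composite gain runs up to 9 points. For a true 5-point composite gain, shared or through MHT visits, power at 1246 patients is about 59-80% by win ratio and 64-76% by two proportions, and lower with clustering. These ranges rest on two-sided 0.05, an unstratified win ratio and the article's 5% and 10% control incidences. At 1500 patients the two-proportion check gives 72-83% without clustering, so the planned size may or may not reach 82% for that effect. The article gives no power figure for that size.

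**What to change.** Restate the power sentence with the effect actually simulated. Say whether the 5 points apply to each component or to the composite, and give the implied composite rate in each arm. From the same simulation, report the power for a true 5-point composite gain at the planned 1500 patients and 600 providers.

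The cost is a rerun of an existing simulation and a short text change, with no extra patients. The downside is a possibly less favourable published figure.
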